### 11.7.2 Analysis of the primary endpoint

The frequencies of the participants with “progression” and their confidence intervals (95%) will be calculated and compared between the treatment groups using Fisher’s exact test.

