| Statistical Rationale         | 
Statistical analyses will be done first “intention to treat” (ITT) followed by “per protocol” (PP) to confirm the results.
 
Primary statistical Analysis:
 
The frequencies of the participants with “progression” and their confidence intervals (95%) will be calculated and compared between the treatment groups using Fisher’s exact test.
 
For group A: Superiority to placebo has to be proven for DOX 200 before testing superiority to placebo for DOX 100. If both tests show superiority to placebo with <math>\alpha = 0.05</math>, non-inferiority of DOX 100 to DOX 200 can be tested in a final step.
 
For group B: DOX 200mg/d will be tested for superiority to placebo with an <math>\alpha</math>-level of 5%.
 
Secondary Endpoints:
 
Secondary endpoints will be described as estimators with confidence intervals (95%) for each intervention group and analyzed with adequate statistical methods.
 
Safety Analysis:
 
Frequency of Adverse events and Serious Adverse Events will be analyzed. In this analysis all patients will be included who took the drugs at least for one day.
 |
| Trial procedures              | 
There will be 15 visits in total (see schedule of activities):
 
Visit 1: Screening
 
Visit 2: Baseline
 
Visit 3: Treatment (42 days)
                                                                                                                                                                                                                                                                                                                                                                                                                                                                                                                                                                                                                                                                                                                                                                                                                                                                                                                                                                                                                            |

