### 11.3 Sample size estimations

#### 11.3.1 Sample size estimations for group A (LE stage 1-3)

- Doxycycline 200mg/d will first be tested for superiority to placebo. When superiority of doxycycline 200mg/d is confirmed, doxycycline 100mg/d will subsequently be tested for superiority to placebo. If both treatment groups rejected their  $H_0$ -hypothesis, they will be tested for non-inferiority. With this subsequent design, a two-sided  $\alpha = 5\%$  can be maintained for all 3 analyses.
- The estimates for progression are based on the results from the previous study by Mand et al. [2] where a progression of 4.9% was seen in the DOX 200 group after 24 months whereas the placebo-treated patients had a progression of 55.6%. The strict control implementation of hygiene measures in this trial may result in a stronger impact of this intervention on both arms. This would result in a smaller margin to verify the added benefit of doxycycline and as a consequence increase the number of patients in the study. In order to account for this influence in the sample size calculations the progression in the placebo group was assumed to be 25% instead of 55%.
- A dropout rate of 30% was assumed.

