## 11.4 Sample size calculation

### 11.4.1 Sample size calculation for group A (LE stage 1-3)

Based on the assumption of a progression in the DOX 200 group of 5% and in the placebo group of 25%, there will be power of 95% to show superiority to placebo if 84 participants are included in each treatment group (+ 30% drop-out rate:  $N = 120/\text{treatment}$ ). Using the subsequent design, superiority of DOX 100 to placebo can be shown with a power  $> 81\%$  if the progression in this group is  $\leq 8\%$ .

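### Group A's primary test is a valid but conservative unadjusted Fisher test, and the >81% power for DOX 100 is the pairwise figure (81.4%); through the sequence it is 79.7%

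*Protocol*

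**What the plan says.** Protocol section 11.7.2 fixes the primary comparison: progression frequencies are "compared between the treatment groups using Fisher’s exact test". The synopsis (Statistical Rationale) says the same. Neither names a covariate or stratum.

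Group A is tested in a fixed order. In the synopsis, "Superiority to placebo has to be proven for DOX 200 before testing superiority to placebo for DOX 100", and non-inferiority of DOX 100 to DOX 200 follows if both succeed. Section 11.3.1 adds: "With this subsequent design, a two-sided $\alpha = 5\%$ can be maintained for all 3 analyses".

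On power, section 11.4.1 assumes 5% progression on DOX 200 and 25% on placebo, and states that "there will be power of 95% to show superiority to placebo if 84 participants are included in each treatment group". It continues: "Using the subsequent design, superiority of DOX 100 to placebo can be shown with a power" above 81%, if progression on DOX 100 is at most 8%.

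The endpoint compares the 24-month stage with the pre-treatment stage (section 7.7.1). Stage is recorded at screening and at enrolment (sections 8.3.1 and 8.3.2), and section 8.1.2 defines the leg to be analysed. Randomization separates Group A from Group B (section 7.6.1); no stratum by individual stage within Group A is stated.

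**The concern.** There are two separate points.

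- **Choice of test.** The protocol allots two-sided 5% to each comparison, but Fisher's exact test with 84 per arm spends clearly less. It also leaves out baseline stage, a plausible prognostic factor that is already recorded for everyone and that the stated randomization does not balance within Group A. Reducing the dose is a primary objective, and DOX 100 against placebo is the weaker of the two superiority tests, so unused power matters most there.
- **Meaning of the stated power.** The DOX 100 sentence in section 11.4.1 invokes the sequential design. Under that design DOX 100 is tested only after DOX 200 has beaten the same placebo arm, so the chance of reaching and winning the second test is lower than the power of that test taken alone. A reader planning around the dose-reduction question needs to know which figure is given.

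**Working it through.** **Inputs.** From section 11.4.1: progression 5% (DOX 200), 8% (DOX 100), 25% (placebo) and 84 evaluable per arm. From section 11.3.1: two-sided 5% per test and 30% dropout (84/0.7 = 120 randomized). From section 11.7.2: Fisher's exact test.

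**Step 1: reproduce the plan's figures.** Let b(x; p) be the binomial probability of x progressions among 84. Pairwise power is the sum of b(x; p_dox) × b(y; 0.25) over all pairs (x, y) with two-sided Fisher p ≤ 0.05.

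- DOX 200 against placebo (5% vs 25%): 95.5%; the plan states 95%.
- DOX 100 against placebo (8% vs 25%): 81.4%; the plan states more than 81%.

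Both reproduce. For 8% vs 25%, the pooled z formula gives 85.0%, the arcsine formula 86.6% and the continuity-corrected formula 79.5%, so exact Fisher is the closest match.

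**Step 2: true size of Fisher.** The same sum with a common rate in both arms:

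| Common rate | Size |
|---|---|
| 5% | 1.7% |
| 10% | 2.9% |
| 15% | 3.0% |
| 20% | 3.1% |
| 25% | 3.35% |
| 50% (maximum) | 3.7% |

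**Step 3: power through the sequence.** For each placebo count y, let A(y) and B(y) be the probabilities that DOX 200 and DOX 100 beat that count. Joint power is the sum over y of b(y; 0.25) × A(y) × B(y) = 79.7%. Given DOX 200 success it is 0.7967/0.9551 = 83.4%. Treating the tests as independent would give 0.9551 × 0.8141 = 77.8%; the shared placebo arm raises this to 79.7%. The step from 81.4% to 79.7% therefore comes from the gate.

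**Step 4: other tests at the same 84 per arm.**

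| Test | DOX 100 alone | Through the sequence | Size |
|---|---|---|---|
| Fisher | 81.4% | 79.7% | 3.35% at 25%; maximum 3.7% |
| Boschloo (Fisher p-value cut-off 0.0633) | 84.5% | 83.0% | 4.3% at 25%; maximum 4.9% |
| Fisher mid-p | 85.8% | 84.6% | 4.7% at 25% |
| Pearson chi-square | 86.4% | 85.1% | 5.07% at 25% |
| Stage-stratified Cochran-Mantel-Haenszel (simulated) | 86.0% to 87.7% | 84.7% to 86.6% | about 4.9% to 5.0% |

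The last row is assumption-dependent, because the protocol gives no stage mix and no stage-specific rates. It assumes equal thirds in stages 1, 2 and 3, placebo rates by stage running from 25/25/25% to 10/25/40%, the same relative effect in each stage, and 100,000 simulated trials per scenario. Against the unstratified chi-square, stratification adds about 0 to 2 points. Most of the gain comes from leaving Fisher's conservatism behind.

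**Step 5: the gain in patients.** Keeping Fisher, 83.0% through the sequence needs 90 evaluable per arm, and 90/0.7 = 128.6, so 129 randomized. About 85% needs 94, and 94/0.7 = 134.3, so 135. Against the planned 120, the choice of test is worth roughly 9 to 15 randomized patients per arm.

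**The case against.** The strongest reply is that nothing here is an error. Fisher controls the type I error, an unadjusted comparison is valid under randomization, and the 84 per arm and both stated powers already allow for Fisher's conservatism. Section 11.3.1 invokes the sequence to justify using the full 5% at each step. Read that way, the DOX 100 sentence means only that no alpha is split, and 81.4% is right. When the DOX 100 test is actually carried out, its power is 83.4%. The joint figure is only about 1.3 points under 81%, and it is already 81.4% if DOX 100 progression is 7.7% instead of 8%. All of this stands, and it makes the point one of efficiency and reporting.

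A reader might infer more than the documents support:

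- *That the sample size was miscalculated, or that Fisher's low size explains the 79.7%.* Both stated figures reproduce with Fisher, and the fall comes from gating.
- *That baseline stage determines who can progress.* On a 7-point scale with stage 7 excluded, every Group A participant can progress. Stage may be prognostic, but the protocol gives no rates by stage.
- *That adjusting for stage brings a large gain.* Anything beyond the unstratified chi-square rests on assumed rates.
- *That the same change suits Group B.* With 30 × 0.7 = 21 evaluable per arm over stages 4 to 6, an even spread leaves about 7 per arm and stage, too sparse for a large-sample stratified test.

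The reply does not remove two things. The test is fixed in the protocol itself, so the choice is open to comment without the statistical analysis plan. And the power sentence names the sequential design while giving a figure that leaves out the gate.

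**Conclusion.** The concern holds in a limited form. Group A's primary test is valid but leaves power unused. At the plan's own rates and 84 per arm, an unstratified exact alternative (Boschloo) raises power through the sequence from 79.7% to 83.0%, and a stage-stratified test raises it to about 85%. The first figure needs no assumption beyond the protocol's. The second carries the stage-mix and stage-rate assumptions listed in the working, but an unstratified chi-square reaches 85.1% without them.

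The stated power above 81% is correct as a pairwise figure. It should not stand as the only figure in a sentence about the sequential design, where the probability that both doses beat placebo is 79.7%. That difference is small, but it takes the dose-reduction objective just below 80%. These changes are worth making before unblinding; the plan is not invalid without them.

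**What to change.** **Group A.** Name one primary superiority test in section 11.7.2, the synopsis and the statistical analysis plan:

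- a Cochran-Mantel-Haenszel test stratified by baseline stage of the analysed leg, with an adjusted risk difference and 95% confidence interval; or
- Boschloo's exact test, if an exact unstratified test is preferred.

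Keep Fisher's exact test as a sensitivity analysis.

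**Group B.** Keep an exact test.

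**Section 11.4.1.** Give both the pairwise and the through-the-sequence power for the chosen test. If Fisher is retained, these are 81.4% and 79.7%; with Boschloo, 84.5% and 83.0%. For the stratified test, state the stage mix and stage rates assumed.

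**Cost.** Wording only, before unblinding: stage is already collected, and section 11.7 leaves the detailed analysis plan to be written before the data file is closed. The one drawback of the stratified test is reliance on a large-sample method with few events. At 5% progression, 84 × 0.05 = 4.2 events are expected in the DOX 200 arm, spread over three strata. The Fisher sensitivity analysis covers this; choosing Boschloo avoids it.

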### 11.7.3 Analysis of the secondary endpoints

Quantitative data will be summarized for each intervention group using the mean, the median, standard deviation, the range (minimum and maximum value), 25th - 75th percentiles and 95% confidence intervals. Qualitative data will be summarized for each intervention group using frequency counts, percentages and 95% confidence intervals. Additionally, box plots or other graphical methods may be used to present the data. The groups will be compared using appropriate statistical methods

### 11.7.4 Safety Analysis

Adverse events (AE) will be assessed in the scope of the daily observed treatment (DOT) and described for each intervention group using frequency counts, percentages and 95% confidence intervals.

## 11.8 Interim Analysis

An interim analysis is planned at each study site when all patients have completed 12 months of follow-up. A decision at 12 months may be taken to terminate the study because of superiority of the doxycycline arm so that the placebo subjects can be treated. Superiority may be defined as non-progression of grade, reduced ADLA, etc. Details of the parameters to be used for the interim analysis will be defined prior to the closing of the database and incorporated in the SAP.

## 11.9 Protocol violations

Protocol violations are major deviations from the procedures outlined in this document like:

- non-compliance with investigational medicinal product (missing treatment days at the end of the treatment period (the treatment period should be prolonged for all days the patient was absent or did not get the trial drugs by decision of the trial clinician),
- intake of medications not allowed
- any non-adherence to the protocol that would have an impact to the subject’s rights, safety or welfare,
- absence from treatment for more than 3 consecutive treatment days (participants who are absent for more than 3 consecutive treatment days will be requested to finish the whole treatment).
- absence from treatment for more than 7 treatment days (treatment will be stopped if participants are absent for more than 7 treatment days, but the patients will be asked to come for the follow-ups).

After a subject has been enrolled, it is the investigator's responsibility to make a reasonable effort to prevent and correct any protocol violations if necessary and to continue the subject's participation in the trial, if possible. Protocol violations will be reported to the sponsor/sponsor delegated person during the course of the trial in the monitoring reports and reported to the Ethics Committees after completion of the trial. All protocol violations will be listed and the impact on the evaluation of the subjects concerned will be discussed prior to statistical analysis.

## **11.10 Handling of Drop-outs, Withdrawal, and Missing Data**

### **11.10.1 Screening failures**

Subjects dropping out of the trial prior to randomization will be listed as screening failures including the reason.

### **11.10.2 Drop-out/Withdrawal after randomization but before treatment start**

Subjects dropping out of the trial after randomization but before start of treatment will be reported including the reason.

### **11.10.3 Drop-out/Withdrawal during or after treatment**

Subjects dropping out of the trial after randomization during but also after treatment will be analysed using all available data (ITT analysis)..

### **11.10.4 Missing treatment days**

Subjects missing more than 3 consecutive treatment days will be analysed using all available data (ITT analysis) but will be excluded from the PP-analysis.

### **11.10.5 Replacement of Patients**

- In case of subjects dropping out in the period between randomization and treatment start additional subjects will be included in the trial. The new participants will be randomized consecutively.
- In case of subjects dropping out during the first 3 days of treatment, additional subjects may be included in the trial. The new participants will be randomized consecutively. All available data from the participants who were treated at least once and later replaced will still be used for the ITT analysis.

## **11.11 Statistical report**

The statistical evaluation and the statistical report will be performed, evaluated and signed by the responsible biometrician. All data in this report will be strictly confidential.

## **12. DATA SAFETY AND MONITORING COMMITTEE (DMSC)**

A single central DSMC will be established with a charter that defines the roles and responsibilities and details of meeting frequency and communications. The DSMC thus established will, in addition to the Authorities/IRBs involved, have a chance to comment on the content of the protocol. The composition, role of the members and the reporting structure are attached as an appendix to this protocol.

Members of the DMSC are:

[name]

[name]

[name]

[name]

[name]

## **13. DEFINITION OF END OF TRIAL**

### **13.1 Regular end of trial**

The regular end of trial is defined as Last Subject Last Visit, meaning, the trial ends when the last patient will be informed about the best performing treatment. At this visit re-treatment will be offered to patient. This re-treatment is not part of the clinical trial but will be performed by the trial clinicians. After regular end or early termination of the trial, patients will be treated according to clinical routine at the discretion of the treating physician.

### **13.2 Termination of the trial for individual subjects**

#### **13.2.1 Termination by the participant**

A patient may decide to withdraw from the study at any time and for any reason. The Investigator should attempt to determine the reason for the subject's decision. There will be no disadvantage for the participant as a result of a withdrawal. If a participant does not return for a scheduled visit, every effort should be made to contact the participant. The investigator should inquire about the reason for withdrawal and the participant should be followed-up regarding any unresolved adverse events, if possible. In any circumstance, every effort should be made to document the participants' outcome. Therefore all participants, even if the participant was withdrawn from the trial treatment, will be encouraged to come for the follow-up visits.

#### **13.2.2 Termination by the investigator**

The investigator may withdraw a patient for any of the following reasons:

- An individual subject's decision.
- Any clinical AE, laboratory abnormality or other medical condition or situation such that continued participation in the study would not be in the best interest of the subject. Subjects will be followed for the duration of the study for indicated safety assessments.
- Non-compliance with study procedures to the extent that it is potentially harmful to the subject or to the integrity of the study data.
- A change in the subject's baseline condition after enrollment so that the subject no longer meets the inclusion/exclusion criteria.

In any circumstance, every effort should be made to document the participants' outcome. Therefore all participants, even if the participant was withdrawn from the trial treatment, will be encouraged to come for the follow-up visits.

### 13.3 Early termination of the entire trial

The IRBs, the GHS-ERC, the Sponsor, the DSMC or the FDA may halt the study at any time following review of any safety concerns independent of the interim analysis and applicable to all centers. Halting the study requires immediate discontinuation of the study agent administered for all subjects and suspension of enrollment until a decision is made whether or not to continue study agent administration.

The halting criteria (as determined by site investigators) for an individual site include:

- two or more subjects experience the same or similar SAEs that are unexpected and are possibly, probably, or definitely related to the study agent

OR

- any safety issue that the site investigators determine should halt the study

The halting criteria (as determined by the study DSMC secondary to aggregate data review) for this study include:

- two or more of the same or similar AE in different subjects that are grade 3 or above and are unexpected and possibly, probably, or definitely related to the study agent

OR

- any safety issue that the study DSMC determines should halt the study

### 13.4 Report of termination of the trial

When the trial is prematurely terminated, the sponsor should submit a report to the IRBs/ FDA within 30 (thirty) days. This report will include:

- Justification for the premature ending or of the temporary halt of the trial;
- Number of patients receiving treatment at the time of the study termination;
- Proposed management of patients receiving treatment at the time of halt or study termination;
- Implications of the discontinuation on the evaluation of the final results.

### 13.5 Notification of the end of the trial

The end of the clinical trial is the date of the last visit of the last participant undergoing the trial. At the end of the trial, the sponsor delegated person will notify the IRBs/ FDA about the trial completion and submit a preliminary report on the ethical evaluation within 30 days and a final report within 90 days after completion of the trial.

## 14. DATA COLLECTION, HANDLING AND RECORD KEEPING

### 14.1 Data Collection methods

The investigator has ultimate responsibility for the accuracy, authenticity, timely collection and reporting of all clinical, safety, laboratory data entered on the Case Report Forms (CRFs). Data will be captured using paper CRF specially designed for the study and approved by the IRBs and FDA. The CRFs must be signed by the investigator or by an authorized staff member to attest that the data contained on the CRFs is true. Any corrections to entries made in the CRFs, source documents must

be dated, signed and explained (if necessary) and should not obscure the original entry. All paper CRFs will be secured in fireproof locking cabinet.

All clinical and laboratory procedures will be performed according to standard protocols governed by GCP and GLP guidelines, 21 CFR Part 11. Tools for qualitative assessments will be made available and validated prior to use.

All study personnel participating will undergo training in the procedures to be used in the study.

A work instruction's manual / manual of SOPs will be prepared at each site and will be made available to all study personnel and study monitors.

## 14.2 Electronic data capture (EDC)

Research data collected on paper CRFs will be transcribed and entered onto the REDCap (Research Electronic Data Capture: <http://project-redcap.org/>) system using double data entry. The EDC application is a secure encrypted web application for building and managing online surveys and databases specifically geared to support data capture for research studies. REDCap meets regulatory requirements for GCP/GCLP, 21 CFR Part 21 and HIPAA compliant with full audit trails capability for tracking data manipulation and user activity, as well as automated export procedures for seamless data downloads to Excel, PDF, and common statistical packages (SPSS, SAS, Stata, R). The equipment for data transfer may include laptops, or mobile applications for tablet computers and/or smartphones with either Android or iOS operating systems. All electronic tools will be password protected.

